##### 1) Anthropometric measures

Waist circumference was measured to the nearest 0.5 cm with an anthropometric tape, at full expiration at the level of the umbilicus. Body height was measured to the nearest half cm, without shoes, using (SECA GmbH, Germany). Body mass was measured barefooted, in light clothing, using an electronic scale (Tanita MC-980MA, Tokyo, Japan). To compensate for the weight of clothes 0,4 kg was withdrawn from the total weight. Based on weight and height the isoBMI was calculated.

##### 2) Body composition

A bio-impedance Tanita scale (Tanita MC-980MA, Tokyo, Japan) was used to estimate muscle mass (kg), body fat (kg and %), bone mass (kg) and the amount of protein (kg).

##### 3) Fitness

Using Jamar handgrip (Jamar Dynamometer, Lafayette, USA) the pupils were instructed to stand firmly on both feet, with a straight elbow keeping the right arm tucked to the body. They were then told to squeeze as hard as possible for 2–3 s. After reading the results, the procedure was repeated. If the pupil misunderstood the instructions or clearly underachieved, a third test was executed. The highest value was recorded. An international reference material are to be used for comparison of results [21].

Balance Y-test (FM-Systems, USA) is based on a set of tests with repeated measurements [22, 23]. The modified test started with the right foot placed on the platform, toes touching the red mark. Starting with a forward push, then a left push and a last push with the left leg crossed behind the right leg. A test was considered approved when the pupil managed to push the block with the toe without leaning on the block or losing the balance after a full stretch. All pupils were instructed and were allowed three trials. Failure to complete a test was marked. The result was measured in centimetres. When analysing the results, the score was divided by age and height of the pupil.

Aerobic fitness was measured using the Andersen intermittent running test in all pupils [24]. Gymnasiums in the attending schools are 20 m wall-to-wall, covered with wooden or rubber floor. The pupils had to touch the wall with one hand, turn around and run back. Music signalled 15 s of running and 15 s of rest during 10 min, giving an overall running time of five minutes. Supervisors controlled the running distance by checking on a form the number of times the pupils run back and forth. After the last lap the length in meters were registered. Subjects were told to run as fast as they could in order to cover the longest possible distance [24].

##### 4) Objective assessment of PA level

An activity monitor (Actigraph wGT3X-BT, ActiGraph LLC, Pensacola, FL, USA) was attached on the hip with an elastic band and worn for 7 consecutive days and nights unless injured, ill or absent. Assessment of activity level will be assessed annually in the same time period to try to ensure the same weather conditions as during baseline testing.

The sampling frequency used was 100 Hz and 10 s epoch. To be included in the analysis, 480 min of registered activity per day was acquired. The minimum of active days was four, and sleep was defined between 22:00–06:00. The intensity domains of sedentary (0–99 counts), light (100–1999), moderate (2000–4999) and vigorous (5000 - _∞_) were used as according to the latest update from ActiGraph LLC, Pensacola, FL, USA. Outcomes for PA levels were mean counts per minute during all assessed minutes as well as time (minutes) spent in different intensity domains (sedentary, light, moderate, vigorous PA). These parameters were investigated in segments of the day (school time, recess, and leisure-time) as class-specific time tables were collected at both assessment periods. These segments were all components in the HOPP intervention and makes it possible to investigate whether the intervention caused any changes in PA during the different segments of the day [8, 18].

##### 5) Blood pressure

Blood pressure is measured automatically (Model M3 Intellisense HEM-7051-E, Omron Healthcare, Kyoto, Japan) on the upper left arm after being seated on a chair for a few minutes. When fail to detect pressure was apparent, a new test was done immediately. After three unsuccessful tests the cuff was attached to the right arm until a successful test was confirmed.

Whenever the result was outside the expected normal age related range, according to the National Heart, Lung and Blood Institute (NIH), USA, up to three new tests were conducted [25]. With results still outside normal range, a re-test was performed at a later occasion. If the values were persistently outside the normal range the values were reported to the HOPP team physician. The physician then contacted the parents and advised them to contact the child’s general practitioner for further follow-up.

##### 6) Blood samples

Blood samples are to be taken annually. However, not all children comply with this procedure. The children were given an opportunity to opt out on the blood sample test, while participating in the other test procedures. Hence, 58.4% (*n* = 1344) of the children completed blood sample procedures in a non-fasting state between 08.00 am and 13.30 pm at baseline. A similar number are expected in 2016.

Groups of four pupils were summoned from the classroom, making sure they had not performed strenuous exercise prior to sample collection. A phlebotomist collected samples in 4 mL tubes (Vacuette® Z Serum Sep Clot Activator and K2E K2EDTA) from the antecubital vein. The gel tubes were end turned and set to 30 min of coagulation before centrifuged at 2000 G for 10 min. Samples were transported to the laboratory and analyzed according to standard procedures. The executive laboratory at Vestfold Hospital Trust is certified according to NS-EN ISO 15189.

Samples were analysed for constituents related to physical capacity, dietary status, cardiovascular risk and inflammation. Ferritin, cobalamin (total vitamin B12) and holotranscobalamin (active vitamin B12) were measured on Architect i2000SR (Abbott Diagnostics, USA) with reagents from the supplier. Total cholesterol, HDL-cholestrol, iron and creatinine were measured on Vitros 5600 or Vitros 5.1 (Ortho-Clinical Diagnostics, USA) with reagents from the supplier. Micro C-reactive protein (mCRP) was measured on Vitros 5600 with reagents from Abbott Diagnostics. Blood counts were measured on Sysmex XE 2100 or XE 5000 (Sysmex, Europe) with reagents from the supplier. Hemoglobin A (HbA1c) test was measured on Tosoh G8 (Tosoh, Japan) with reagents from the supplier.

Blood samples were not taken fasting; hence triglycerides were not sampled. We were therefore not able to use Friedmans formula for estimating Low-density Lipoprotein Cholesterol (LDL-C). As a substitute non HDL-C were used (Serum cholesterol – HDL = non HDL-C) [26].

Any result outside the normal range, according to the laboratory at Vestfold Hospital Trust reference material used in the outpatient clinic, was reported to the team physician. He again contacted the parents to give appropriate advice, usually a follow-up at the child’s general practitioner.

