## Methods/design

### Study population and inclusion criteria

The HOPP study is a controlled longitudinal school-based PA intervention. Seven elementary schools in Horten municipality, Vestfold County, Norway are intervention schools. Two control schools in Akershus County, Eiksmarka school (*n* = 520) and Rasta school (*n* = 465), were included. The control schools were recruited based on estimated socioeconomic level, using a centralised Norwegian program for systematic quality work in schools and kindergartens called PULS. This represent a total population of 2817 pupils of which 1815 children received the intervention as a part of the pedagogical platform in Horten municipality. All children were invited to be part of the research project. Based on recruitment procedures a total baseline participation of 2297 pupils (82%) was achieved. The children were recruited from 1^st^ - 6^th^ grade (age 6–11 yrs) (Table 1).

**Table 1 Tab1:** Baseline population for all grades as of 2015 is shown, as well as the sample size, based on children whose parents gave consent to participation in the research project

Grades	1	2	3	4	5	6	Total
Population	457	484	457	462	461	496	2817
Sample	351	381	370	389	381	425	2297
Intervention schools	248	264	229	264	269	271	1545
Control schools	103	117	141	125	112	154	752

The sample size is divided into intervention and control schools

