**Fig. 2 Fig2:**
[figure not shown]
Estimated number of pupils tested annually, assuming no dropouts. Dark grey is intervention schools, light grey control schools

**Table 2 Tab2:** Test variables for HOPP

Annual test methods	Grades
Activity & health	
Physical activity monitoring	All
Fitness tests^b^	All
Oxygen uptake^c^	1^st^
Blood samples^d^	All who volunteered
Learning & cognition	
Erikson Flanker test	2^nd^
Stroop test	4^th^, 5^th^ & 6^th^
Academic national tests	5^th^
Nutrition and growth	
Diet (“Ungkost 2000”)	4th
Anthropometry	All
Body composition^a^	All
Mental health	
Life Quality in Children and Adolescents (ILC)	All
Strengths and Difficulties Questionnaire (SDQ) (2016)^e^	6^th^ & 7^th^
Self-Perception Profile for Adolescents (SPPA) (2016)^e^	6^th^ & 7^th^

^a^= Using Tanita bio-impedance measurements.

^b^= Fitness tests include endurance test (Andersen test), strength (handgrip) and balance.

^c^= Oxygen uptake was performed on 1st grade pupils only as it is very time consuming.

^d^= Blood samples include serum cholesterol, High-density Lipoprotein (HDL), Ferritin, Iron, Cobalamin (total vitamin B12), Holotranscobalamin (active vitamin B12), Creatinine, HS-CRP, blood count, Haemoglobin, Hematocrit and HbA1c.

^e^= SDQ & SPPA are tested as of 2016.

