### Children’s test

#### Annual measurements for all participants

Measurement of ^1)^ anthropometry, ^2)^ body composition, ^3)^ fitness and ^4)^ PA level, ^5)^ blood pressure, ^6)^ blood samples and ^7)^ The Inventory of Life Quality in children and adolescents (ILC) are to be completed annually for all participants (Table 3). The protocol design allows for baseline analyses, interventional one-year effect analyses, analyses of secular trends and longitudinal effect analyses across the full length of the study. Due to being very time consuming oxygen uptake is restricted to pupils born 2008 (1^st^ grade in 2015).

**Table 3 Tab3:** Based on the various power tests, the following sample size (intervention and controls schools) was calculated, with a beta of 80% and alpha of 5%

Test area	n
Anthropometry	64^b^
Cardio-metabolic risk factors	126^c^
Physical activity level	73^a^
Aerobic capacity	10^a^
General physical capacity	126^c^
Blood tests	34^a^
Quality of life	73^a^
Diet	24^a^
Cognitive ability	85^a^
Academic performance	34^a^

Statistical program: Systat 13, Power Analysis. ^a^One-sample t-test, ^b^Two-sample t-test, ^c^Z-score

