#### Main outcome measure

In the present study cardio-metabolic risk factors were calculated by integrating objective measurements of BMI, waist circumference, muscle mass, percentage fat, endurance test, total serum cholesterol, HDL, non-HDL, mCRP and HbA1c. Firstly, all variables were divided into quartiles. Secondly, the results were dictomised as the children in the quartile of highest risk factor were given the score 1, and the children in the other quartiles were scored 0. Thirdly, children categorise with risk factors were assigned to one of 11 risk factor categories, 0–10, depending on their number of risk factors. Fourthly, the probability of children having 0 to 10 risk factors were calculated using the binominal probability formula (*n*! • *p*
^r^ • (1 – *p*)^*n-r*^ / (*r*! • (*n*-*r*)!) [49]. Where *n* is the possible number of risk factors (total of 11), *p* is the probability of having a risk factor (highest risk factor quartile: 0.25) and *r* is the number of risk factors for which the probability is calculated (0–10) [17]. Fifthly, the observed number of children in each group was compared to the expected number by calculating the ratio and plotting with a 95% confidence interval. Finally, a composite cardio-metabolic risk factor profile was calculated using Z-scores by age and gender for selected risk factors. The Z-scores were then summed for each individual regarding the individual risk factors to create the clustered risk score [17].

The occurrence of cardio-metabolic risk factors in the HOPP study was calculated at baseline. In addition, the calculus is to be computed annually to reveal any change in cardio-metabolic risk factors as a result of the intervention.

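### Half of the main composite's ten components need blood, so it can be complete for at most 1344 of 2297 children, too few for the adequacy statement by grade and sex

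*Protocol article*

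**What the plan says.** All references are to the protocol article.

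- **Main outcome measure** names ten components: BMI, waist circumference and muscle mass, followed by "percentage fat, endurance test, total serum cholesterol, HDL, non-HDL, mCRP and HbA1c". Each is cut into quartiles. The highest-risk quartile scores 1 and "the children in the other quartiles were scored 0". Children are placed on a single 0-10 scale and the observed counts are compared with one binomial distribution. A sum of Z-scores over selected, unnamed factors follows. The calculation was done at baseline and is to be repeated each year.
- **6) Blood samples** makes blood optional: "The children were given an opportunity to opt out on the blood sample test, while participating in the other test procedures". It reports that "58.4% (*n* = 1344) of the children completed blood sample procedures" and adds: "A similar number are expected in 2016". It also defines non-HDL as serum cholesterol minus HDL, so that component needs blood as well.
- **Table 2** gives the coverage of blood sampling as "All who volunteered".
- **Annual measurements for all participants** lists blood among seven measurements that "are to be completed annually for all participants".
- **Study population and inclusion criteria** gives the denominator: "a total baseline participation of 2297 pupils (82%) was achieved".
- **Intervention analyses** declares the sample large enough for every variable at every age, including within each gender, and points to Table 3. That table gives 126 for cardio-metabolic risk factors.

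**The concern.** The outcome definition and the sampling scheme do not fit each other. Half of the components are unavailable for a known group of about two children in five, and the article expects this to recur in 2016. Yet the main outcome is described on one scale, with one binomial expectation, as if every participant could be placed on it. Nothing in that section says that the count covers only blood-sampled children.

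Two things are at stake. First, the evidence for the main outcome comes from a smaller, self-selected group, while the abstract shows 1545 and 752 children. Who accepted venepuncture may differ between arms, since the municipality ran an information campaign in Horten and the control schools were told nothing about the programme (Information and recruitment). Second, the statement that the sample suffices by age and gender was made without allowing for this loss.

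**Working it through.** **Inputs.** 2297 participants, 1545 intervention and 752 control, with grade totals 351, 381, 370, 389, 381 and 425 (Table 1). 1344 children with blood (6) Blood samples). Ten components (Main outcome measure). 126 children for cardio-metabolic risk factors (Table 3).

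**1. The article's own figure.** 1344 / 2297 = 58.5%, against 58.4% printed. A printed 58.4% would need a denominator of about 2300 to 2303, so the gap is immaterial. Without blood: 2297 − 1344 = 953 children, or 41.5%.

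**2. Share of the composite that needs blood.** Total cholesterol, HDL, non-HDL, mCRP and HbA1c: 5 of 10. The binomial step prints 11 possible factors although ten are listed; the abstract reaches eleven by adding physical activity level. Blood would then be 5 of 11, and the conclusion is the same.

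**3. Ceiling for the full composite.** At most 1344 children at baseline, and fewer if a non-blood component is also missing. The paired 2015-2016 comparison (Analyses of effect) needs blood in both years, so its number cannot exceed 1344 either. If uptake is equal in the arms (assumed, because the split is not given): 1545 × 0.585 ≈ 904 and 752 × 0.585 ≈ 440.

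**4. Adequacy by grade and gender.** Table 3 does not say clearly whether 126 is per group or for both groups together. The reading kinder to the plan is the total.

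- Without the blood loss and with an even sex split (assumed), a grade-by-sex cell holds 351 / 2 = 175.5 to 425 / 2 = 212.5 children. All cells pass 126.
- With 58.5% uptake in every grade: 351 × 0.585 / 2 ≈ 103 in the smallest grade and 425 × 0.585 / 2 ≈ 124 in the largest. All cells fall short of 126.
- Uptake needed to reach 126: 126 / 212.5 = 59.3% in the largest grade, rising to 126 / 175.5 = 71.8% in the smallest.
- Without either assumption: six grades by two sexes is 12 cells, and 12 × 126 = 1512, which exceeds 1344. However uptake and sex are distributed, not every cell can reach 126.
- By grade alone, the total reading is met: 351 × 0.585 ≈ 205 to 425 × 0.585 ≈ 249. On the per-group reading it is not, because the control grades would hold about 103 × 0.585 ≈ 60 to 154 × 0.585 ≈ 90 children.

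**5. Passages side by side.** The overview of annual measurements has blood completed for all participants. Table 2 restricts it to volunteers, and the blood section reports 58.4%. The first cannot stand with the other two.

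**The case against.** The strongest reply is that this is only unstated handling of missing data, which belongs in a full protocol or analysis plan that is not shown. That disposes of any complaint that an imputation method is absent. It does not dispose of the printed contradiction on who gives blood, or of a printed adequacy statement that the article's own numbers do not support.

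A reader might infer that children without blood are scored 0 on five components and so look low-risk, and that a difference in blood uptake between arms would then pass for a programme effect. The article does not support this. A child with no value falls in no quartile, so the rule gives neither 1 nor 0. No uptake by arm is reported, so the size of any such shift would rest on an invented gap. Even then, a gap that stays the same from year to year would largely cancel in the planned comparisons of change from baseline.

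Three further points carry weight. The blood section openly reports incomplete uptake, so the limit is disclosed and the overview sentence may be loose wording. The Z-score sum uses unnamed factors and might leave blood out; the ceiling is firm only for the 0-10 count. And the 126 cannot be reproduced, because no standard deviation or difference is given for it; it is used here only as the article's own benchmark.

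**Conclusion.** The point holds in this form. The ten-component count, as defined, can be complete for at most 1344 of 2297 children (58.5%) at baseline. The same applies to the Z-score sum if blood markers are among its factors. On the evident complete-case reading, the main composite describes children who volunteered for blood sampling, not the full consenting sample.

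The adequacy statement does not hold for the full composite by age and gender: about 103 to 124 children per grade and sex in both arms together, against 126. Those cell sizes assume equal uptake across grades and an even sex split. That at least one cell falls short does not depend on either assumption. The shortfall per cell is modest; the narrowing of the analysed population is the weightier part. The documents do not show bias between the arms, and none is claimed here.

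**What to change.** 1. State that the ten-component count and its binomial comparison are computed only in children with all components measured.
2. Give 1344 as the baseline ceiling for the main composite, with the split by arm, and restrict the adequacy statement to what that number supports.
3. Add a supportive score from the five non-blood components, with its own binomial number of factors, in all consenting children.
4. Report blood uptake by arm and year, and compare donors with non-donors on the non-blood components.
5. Say whether the Z-score sum includes blood markers.
6. Correct the overview of annual measurements so that it agrees with Table 2 and the blood section.

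Multiple imputation of the blood components may serve as a sensitivity analysis. It need not be the main one, since it would fill five markers for 41.5% of children.

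The cost is a smaller headline number for the main outcome, a few changed sentences and a little extra analysis. No new data are needed.

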##### 7) Quality of life (ILC)

A Norwegian version of the generic 7-item Inventory of Life Quality in Children and Adolescents (ILC) was used to assess various quality of life (QoL) parameters over the past week [27, 28]. The ILC includes a global QoL and scores seven items; school performance, family relations, peer relations, autonomy in play, physical health, mental health and a global assessment of wellbeing [29]. The children’s version of the ILC was completed on a hard copy form, under supervision. The test supervisors were trained in giving instructions for each question according to the ILC-manual.

##### 8) Oxygen uptake

Only pupils born 2008 are to be tested for oxygen uptake annually until 2021 as oxygen uptake procedures require use of highly sophisticated instruments for field-testing and is time consuming. By obtaining seven consecutive years of data, longitudinal measurement of physiological development across childhood will be available. In addition, the design permits comparison between intervention (*n* = 248) and control (*n* = 103) schools for all years.

The oxygen uptake test at baseline was performed on a treadmill (Matrix T3xe, USA) measuring peak oxygen uptake (VO_2peak_), respiratory rate (RR), respiratory exchange ratio (RER), peak ventilation (VE_peak_), peak heart rate (HF_peak_) and time to exhaustion using a portable metabolic analyzer, Cosmed K4b^2^,(Cosmed S.r.l., Roma, Italia). A Hans Rudolph V2 oro-nasal facemask (Hans-Rudolph, Shawnee, KS, USA) was used during testing. The protocol in use had a start load of 5 km/h – 5% incline for 5 min. The speed was increased to 7 km/h, and further by 1 km/h every minute until reaching 10 km/h. After this point, a 1% increase in incline was applied every minute until fatigue [30, 31]. Breath by breath results was averaged to 30 s intervals and the highest 30 s value near the end of the test was considered the VO_2peak_. As test termination criteria for adults are difficult to achieve for children, the children’s unwillingness to continue was used as an indication of VO_2peak_ [32].

### Tests not taken annually

Due to time restraints, suitability and validation some tests were conducted only at specific ages. Eriksen Flanker test for executive functions is validated up to 3rd grade. Older pupils used the Stroop test. Also, the Strength and Difficulties Questionnaire (SDQ), Self-Perception Profile for Adolescents (SPPA), the nutrition test and academic performance, were all used in specific age groups. Effects of the intervention will be investigated in regards to these test outcomes as well as secular trends over time. Also, the results will be compared to reference materials.

#### Eriksen flanker test

The Eriksen Fish Flanker test (Millisecond Software, Seattle, Washington, USA) was used to assess executive function at specific ages (Fig. 4) [33]. A total of 120 experimental trials, 60 compatible and 60 incompatible trials, were completed after practice. The trial types appeared randomly and were equally likely to occur. The children had one minute break after every 40 trials [34]. The outcomes measures are reaction time and accuracy (percentage of possible trials where the correct response was selected). Calculation of interference scores (incongruent – congruent) for both reaction time (RT) and accuracy will allow for interpretation of the flanker effect as the difference in speed and accuracy of information processing [35].

